#### Secondary endpoints

Continuous variables including length of stay in hospital, length of mechanical ventilation and seven-day organ failure will be reported as mean and standard deviation or as median and interquartile range, and compared between the two groups using Wilcoxon tests. Dichotomous variables including in-hospital mortality, nosocomial infections, adverse events of intervention, failure of mechanical ventilation and improvement of oxygenation will be reported as absolute and relative frequencies, and compared with the χ^2^ test between the two groups. Similar subgroup analysis procedures described above for primary endpoint will also be used. Kaplan-Meier estimator will be used to compare median hospital and ICU length of stay between the two groups. The event of interest and the censoring event are discharge alive and death, respectively. Intubation rate in NIV group and weaning rate in IMV group will be reported as absolute and relative frequencies. Independent variables associated with intubation rate and weaning rate will be explored with Logistic analysis model with a *p* < 0.03 in a step-by-step, backward-forward approach. In accordance with our hypothesis, the ventilatory approach and disease severity will be both forced in the model.

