## Background

Immunocompromised patients has increased subtantially over recent decades because of the epidemic of Acquired Immune Deficiency Syndrome (AIDS), common use of solid and hematologic transplantation requiring subsequent immunosuppressive therapy, better and thus greater use of iatrogenic immunosuppression, and improved survival due to better health care conditions [1]. Infection, especially pulmonary infection, is still one of the most common complications of immunosuppression [1]. Acute respiratory failure (ARF), especially when induced by sepsis, is the leading cause of ICU admission in immunocompromised patients, with a case fatality, between 30% and 90%, despite the use of antimicrobial agents and preventive measures [1–6].

Noninvasive mechanical ventilation (NIV) and invasive mechanical ventilation (IMV) are two fundamental treatment ways to provide supplemental oxygen and ventilatory support for patients with relatively severe ARF. NIV is the delivery of positive pressure ventilation via oronasal or nasal airway, a total face mask or helmet rather than endotracheal tube. The most common types of NIV are continuous positive airway pressure (CPAP) and bi-level positive airway pressure (BIPAP). By avoiding invasive intubation or tracheostomy, NIV keeps an intact upper airway and therefore retains airway defense mechanisms, which is important for immunocompromised patients who are especially vulnerable to nosocomial infections. Common complications caused by intubation such as aspiration pneumonia, ventilator-associated diseases, and trauma to adjacent organs could thus be avoided by NIV [7, 8]. NIV is now generally considered as the first-line intervention for several ARF subtypes [9–11], including chronic obstructive pulmonary disease (COPD), asthma, cardiogenic pulmonary edema and other situations [12]. However, NIV is not appropriate for all forms of ARF. In ARDS patients, for instance, the use of NIV is controversial and lacking high-quality of evidence [13–16]. Another oxygen therapy named high-flow oxygen therapy is getting more and more attention in critical care. Recent studies showed high-flow oxygen therapy obtained a comparable or even better prognosis in ARF patients [17–19]. However, it requires more advanced equipment, thus not as popularized as other conventional oxygen therapies especially in developing countries.

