### Sample size

The hypothesis of the present trial is that 30-day all-cause mortality in patients treated with NIV will be lower than those treated with IMV. According to previous studies, the mortality rate of ARF immunocompromised patients is from 30% to 90% [1–4]. We used the data from the Fig. 4 of our previous meta-analysis to calculate the sample size, i.e. 30-day mortality in IMV-treated patients of 125/168 (75%) [21], and 85/168 (50%) [21] in NIV-treated patients, 88 patients are needed in each group to establish non-inferiority with 90% power and a 1-sided 5% type I error rate. Assuming that 25% of patients would be lost after the enrollment, thus at least of 236 patients are required.

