#### Data collection and follow-up

Baseline characteristics will be recorded immediately after inclusion, including age, gender, primary diagnosis, PaO_2_/FiO_2_, causes of ARF and immunocompromised status, preexisting comorbidities, SAPS II, oxygen therapy and other treatment used before the inclusion. The information required for evaluation during study participation will be recorded daily until primary endpoint occurs or until day 30 after inclusion, whichever occurs first. Evaluations include settings of intervention, other treatment, laboratory data, evaluation of ARF, adverse events of intervention and complications developed during hospital stay. Each patient is followed until day 60 or until other endpoints occur, whichever occurs first. The following data are recorded: 30-day survival, length of hospital stay, hospital survival and adverse events of intervention.

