#### Interim analysis

Considering a large estimated sample size, two interim analyses are scheduled. Sample sizes of 176 achieve 90% power to detect a difference of 0.25 between the group proportions of 0.50 and 0.75 at a significance level (alpha) of 0.05 using a two-sided z-test with continuity correction. Assuming a dropout rate of 25%, the subjects were required to be 236. The O’Brien-Fleming spending function will be used to determine the test boundaries for 3 sequential tests (Nominal Alpha = 0.000207, 0.012025, 0.046259) [36]. One interim analysis is scheduled after enrollment of 39 patients in both group, and the second analysis after another enrollment of 39 patients in both groups. The independent data and safety monitoring committee (DSMC) consists of one biostatistician and two physicians independent of the present trial. For both interim analyses, the DSMC will monitor and assess results on day 30 mortality, failure of NIV, severe complications and seven-day organ failure as indicated by the SOFA scores. The results of the interim analyses will be kept closed unless DSMC requests premature trial termination based on these results. If the difference of the main outcome, mortality was found statistical difference between groups, then discontinuation ahead will be applied.

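### Nosocomial infection is compared only as a crude proportion by chi-square, so with mortality planned at 75% v 50% the result mixes infection risk with time alive in hospital

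*Protocol article*

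**What the plan says.** In the protocol article, Statistical analysis, Secondary endpoints, "Dichotomous variables including in-hospital mortality, nosocomial infections, adverse events of intervention, failure of mechanical ventilation and improvement of oxygenation" are reported as frequencies and compared between arms by chi-square. No time at risk and no rule for death or discharge is attached to infection. The same paragraph does use a time-to-event method for length of stay, with death as the censoring event.

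Under Data collection and follow-up, daily information, including complications during the hospital stay, is "recorded daily until primary endpoint occurs or until day 30 after inclusion", whichever comes first. The primary endpoint is death, so a patient who dies early without infection counts as uninfected.

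The mortality gap is a planning assumption. Interim analysis states: "Sample sizes of 176 achieve 90% power to detect a difference of 0.25 between the group proportions of 0.50 and 0.75". Sample size takes the same rates from 125/168 on IMV and 85/168 on NIV.

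Background gives part of the reason for interest in this endpoint: NIV leaves airway defences intact, "which is important for immunocompromised patients who are especially vulnerable to nosocomial infections".

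**The concern.** The Background argument is about the risk of infection while a patient is alive and ventilated. The chi-square null is different: equal proportions ever infected before death, discharge or day 30. That proportion depends on the daily infection risk and on how many days patients stay at risk. Under the trial's own mortality figures IMV patients have fewer such days unless discharge offsets it, so the arm that keeps more patients alive has more opportunity to record an infection.

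An apparent excess of infection on NIV could then be a by-product of better survival, and a real reduction in daily risk could be hidden. Either would be misread if the chi-square result were reported as a statement about infection risk.

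**Working it through.** **The plan's own figure.** For 0.75 v 0.50, two-sided 0.05 and 90% power, the uncorrected size is [1.96√(2·0.625·0.375) + 1.2816√(0.1875 + 0.25)]²/0.25² = 76.7 per arm. Continuity correction gives 85, or 87 at the final sequential level of 0.046259, against 88 stated. Then 88/0.75 = 117.3, so 118 per arm and 236 in total. (Sample size describes the same 88 as a one-sided non-inferiority calculation. That conflict is a separate matter and leaves the mortality inputs unchanged.)

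**Inputs.**
- From the document: 30-day mortality 0.75 (IMV) and 0.50 (NIV); 118 per arm, or 88 after the assumed 25% loss; test level 0.05; recording to death or day 30.
- Assumed, because the document gives none: constant hazards; daily infection hazard L = 0.01, 0.02 or 0.04; daily hazard of discharge alive d = 0.005 or 0.01, equal in both arms.

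**Formulas.**
1. Death hazard m solves m/(m+d)·(1 − exp(−30(m+d))) = 0.75 or 0.50.
2. Proportion infected p = L/(L+m+d)·(1 − exp(−30(L+m+d))).
3. Chi-square power in one direction = Φ((|D| − 1.96·s0)/s1). D is the difference in proportions, s0 its pooled and s1 its unpooled standard error.
4. Hazard-test power (Schoenfeld) = Φ(√(E/4)·|ln 0.5| − 1.96), with E the expected number of infections.

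**One setting in full (L = 0.02, d = 0.01, 118 per arm).** Step 1 gives m = 0.0596 on IMV and 0.0279 on NIV.
- IMV: 0.02/0.0896·(1 − exp(−2.69)) = 0.208.
- NIV, equal daily risk: 0.02/0.0579·(1 − exp(−1.74)) = 0.285.
- NIV, risk halved: 0.01/0.0479·(1 − exp(−1.44)) = 0.159.
- Equal risk: D = 0.0765, s0 = 0.0561, s1 = 0.0559. Φ((0.0765 − 0.1100)/0.0559) = Φ(−0.60) = 0.275, towards more infection on NIV.
- Risk halved: D = 0.0489, s0 = 0.0504, s1 = 0.0503. Φ((0.0489 − 0.0988)/0.0503) = Φ(−0.99) = 0.16.
- Hazard test, risk halved: E = 118·(0.208 + 0.159) = 43.3. Φ(3.29·0.693 − 1.96) = Φ(0.32) = 0.63.

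**All six settings.**

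| L | d | IMV v NIV infected, equal risk | Significant, 118 (88) per arm | NIV infected, risk halved | Chi-square detects, 118 | Hazard test detects, 118 |
|---|---|---|---|---|---|---|
| 0.01 | 0.005 | 12.9% v 17.4% | 16% (13%) | 9.2% | 14% | 42% |
| 0.01 | 0.01 | 11.4% v 15.9% | 17% (14%) | 8.4% | 12% | 39% |
| 0.02 | 0.005 | 23.3% v 30.9% | 26% (21%) | 17.4% | 20% | 67% |
| 0.02 | 0.01 | 20.8% v 28.5% | 28% (22%) | 15.9% | 16% | 63% |
| 0.04 | 0.005 | 38.8% v 49.9% | 40% (32%) | 30.9% | 25% | 88% |
| 0.04 | 0.01 | 35.1% v 46.4% | 42% (33%) | 28.5% | 20% | 85% |

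Nearly all significant results at equal risk point to more infection on NIV.

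**Sensitivity to discharge.**
- Faster but equal discharge, d = 0.03 in both arms, L = 0.02: m = 0.0984 and 0.0398, so p = 0.133 v 0.208. Φ((0.0745 − 0.0960)/0.0487) = Φ(−0.44), about 33% significant. The bias persists.
- Survivors in both arms leave between days 10 and 30 (L = 0.01-0.05, 88-118 per arm): 13.7 v 16.6 mean days at risk. The excess on NIV is significant in 6-21%, and a halving is detected in 17-51%.
- NIV patients leave twice as fast, 2% v 4% up to 5% v 10% per day: 9.8 v 10.7 days at risk narrowing to 5.0 v 5.0, and rejection at equal risk is about 5-6%.
- NIV survivors leave on days 7-20, IMV survivors on days 20-30: 15.0 v 13.4 days at risk. The observed proportion is higher on NIV in only 35-41% of trials, and a halving is detected in 36-89%.

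**The case against.** The strongest reply concerns discharge. Background cites prior evidence that NIV shortened stay as well as lowering mortality and infection, mainly in less severe patients and certain subgroups. Faster discharge on NIV therefore belongs to the same hypothesis as lower mortality. The settings in the table also assume slow discharge: at 0.5-1% per day, 64-80% of NIV survivors are still in hospital at day 30. This stands as a limit on size and direction. It does not rescue the test, because the crude result then moves with discharge timing instead, with daily infection risk unchanged.

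Second, chi-square is a valid intention-to-treat comparison of the proportion ever infected. That is correct, so there is no case for calling it invalid. The fault lies in using it alone to speak about infection risk.

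Third, the hazard test has limits of its own. It compares patients still alive and in hospital; if NIV keeps sicker, more infection-prone patients alive, the comparison is selected. That it holds its nominal level when simulated daily risks are equal is true by construction. At a 1% hazard it too misses a halving more often than not (39-42% power at 118 per arm).

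Fourth, infection is one of many secondary endpoints and one of several reasons given for NIV, alongside avoiding aspiration pneumonia, ventilator-associated disease and trauma to adjacent organs. Neither the primary analysis nor the sample size depends on it.

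**Conclusion.** The point holds in a limited form. As planned, the only comparison of nosocomial infection mixes infection risk with time alive in hospital, in a trial that expects mortality of 75% v 50%. With similar discharge in both arms, equal daily risk tends to give a higher observed proportion on NIV. On the assumptions tabulated this is significant in about 16-42% of trials at 118 per arm (13-33% at 88), and a true halving is found in 12-25% by chi-square against 39-88% by a hazard test.

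A reader might infer that the planned test will usually declare more infection on NIV, or is always biased against NIV. The document supports neither. A significant excess is a minority result even in these settings, and the document supplies no infection rate, death timing or discharge timing. Clearly faster discharge on NIV shrinks, removes or can reverse the bias. Part of the low power is also simply few infections. The change is worth making because it is cheap and alters what can be concluded about infection risk; the primary result is untouched.

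**What to change.** In Statistical analysis, Secondary endpoints:
- Keep the proportion infected as a descriptive result, shown as cumulative incidence by arm with death and discharge alive as competing events.
- Add a comparison of time from randomisation to first nosocomial infection by cause-specific hazard (log-rank or Cox, stratified by centre where feasible), with death and discharge ending time at risk.
- State that conclusions about infection risk rest on both results, read together with mortality, and that the hazard comparison is made among survivors and needs cautious reading.

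Cost: the date of first infection, which daily recording to day 30 should already supply, and two figures to report and interpret instead of one. Sample size, treatment and visits do not change.

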### Statistical analysis

All data will be analyzed based on the intention-to-treat (ITT) principle. All analysis results and findings will be reported according to CONSORT statement recommendations [37]. Descriptive statistics will be used to comparing the baseline features of the groups established by randomization. All tests will use a significance level of 0.05 and be performed using SAS 9.4 (TS level 1 M2; Cary, NC, USA).

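### Kaplan-Meier medians for hospital and ICU stay censor deaths, although death is a competing event; the parallel Wilcoxon test on hospital stay has no stated rule for deaths

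*Protocol article*

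**What the plan says.** Under Statistical analysis, Secondary endpoints, the protocol article gives hospital stay two analyses.

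- **Rank test.** Hospital stay, ventilation time and the seven-day SOFA outcome are treated as continuous and are to be "compared between the two groups using Wilcoxon tests". No value or rank is given for a patient who dies.
- **Kaplan-Meier.** "Kaplan-Meier estimator will be used to compare median hospital and ICU length of stay between the two groups". The next sentence fixes the coding: "The event of interest and the censoring event are discharge alive and death, respectively".

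The opening of Statistical analysis adds "All data will be analyzed based on the intention-to-treat (ITT) principle". Ventilator-free days appears in the list of secondary endpoints under Study outcomes, but the analysis section names no method for it. The planning mortality is 75% with IMV and 50% with NIV (Sample size; Interim analysis).

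**The concern.** Censoring is harmless when a censored patient could still have the event later, at the same rate as those still under observation. A dead patient cannot be discharged alive. Treating death as censoring therefore estimates how long discharge would take if death were abolished. With half to three quarters of patients expected to die, that is far from what happens on the ward.

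The rank test raises a separate issue. If all randomised patients enter with their raw days, a death on day 5 ranks as a better result than a discharge on day 20.

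Shorter hospital and ICU stay is part of the trial's rationale (Abstract; Background), so readers will look at these results. A misleading median, or two analyses of one endpoint that disagree, would weaken what the trial can say about stay.

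**Working it through.** **Inputs from the article.** Planning rates: 125/168 = 74.4%, used as 75% (IMV); 85/168 = 50.6%, used as 50% (NIV). Size: 88 per group; 88/(1 − 0.25) = 117.3, rounded up to 118, and 2 × 118 = 236, as stated. With 88 per group, a two-sided 5% z-test with continuity correction has about 91% power for 0.50 v 0.75, consistent with "Sample sizes of 176 achieve 90% power to detect a difference of 0.25 between the group proportions of 0.50 and 0.75". The article gives no figure for stay or for time to death, so every duration below is an assumption.

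**Step 1: can the median be reached?** If deaths precede discharge, at most 1 − 0.75 = 25% of IMV patients and 1 − 0.50 = 50% of NIV patients are ever discharged alive. A median needs 50%. In the IMV arm it does not exist once more than half of the patients die before discharge, that is, once more than 0.50/0.75 = two thirds of the planned deaths do so. In the NIV arm it sits at the edge.

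**Step 2: Kaplan-Meier with constant hazards.** Assume a discharge hazard λ = 0.04/day in both arms and death hazards h = 0.12 (IMV) and 0.04 (NIV). Eventual mortality is h/(λ + h) = 0.75 and 0.50.

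- Kaplan-Meier median, death censored: ln 2/0.04 = 17.3 days in both arms.
- 1 − KM at day 30: 1 − exp(−0.04 × 30) = 69.9% in both arms.
- True proportion discharged alive by day 30: λ/(λ + h) × [1 − exp(−(λ + h) × 30)].
  - IMV: 0.25 × [1 − exp(−4.8)] = 24.8%
  - NIV: 0.50 × [1 − exp(−2.4)] = 45.5%

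Kaplan-Meier shows no difference where the true difference is about 21 percentage points. A log-rank test rejected in about 4% of simulated trials.

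**Step 3: Kaplan-Meier when survivors leave later than decedents die.** Assume the same survivor stay in both arms (lognormal, median 25 days, log-SD 0.5, capped at day 60) and deaths within 30 days with median 8 days. Kaplan-Meier medians are about 30 (IMV) and 27 (NIV) days. Both exceed the survivors' median of 25, and they differ although survivors' stays are identical.

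**Step 4: Wilcoxon on raw days, all patients, two-sided 5%.** Same model, 75% v 50% mortality, 118 per arm:

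| Survivor / decedent median (days) | Trials significant |
|---|---|
| 30 / 8 | about 82% |
| 25 / 8 | about 75% |
| 20 / 12 | about 35% |
| 15 / 8 | about 36% |
| 15 / 12 | about 10% |
| 15 / 15 | about 6% |

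In the 25/8 case every significant result had the shorter stay in the high-mortality arm. At 88 per arm that case gives about 60%. When deaths come as late as discharges, the effect all but vanishes.

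**Step 5: the two analyses together.** In the 25/8 case, in roughly three quarters of trials the raw median was shorter with IMV while the Kaplan-Meier median was longer with IMV. The article does not say which analysis takes precedence.

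**Step 6: ventilation time.** Same mortality, 118 per arm. With survivor median 5 days and decedent median 10, the Wilcoxon test rejects in 28% of trials, all with longer ventilation in the high-mortality arm. With 8 and 8 days it rejects in about 4%. The sign depends on whether survivors are weaned sooner or later than decedents die.

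**The case against.** **The Wilcoxon part rests on silence.** The article does not say that deaths count as short stays. ITT makes their inclusion likely but does not fix their value; survivors only or worst rank remain possible, and an analysis plan not shown may set the rule. The same holds for the seven-day SOFA comparison when a patient dies first. This stands: for the rank tests the fault is an unstated rule, not a stated error. It does not reach the Kaplan-Meier analysis, where the coding of death is explicit.

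**Stronger readings that the documents do not support.**

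- A reader might infer that ventilation will look shorter in the arm with more deaths. Step 6 shows that the direction is open. Kaplan-Meier is planned only for hospital and ICU stay, and ventilator-free days is already a listed endpoint.
- A reader might infer that both analyses of stay flatter the arm with more deaths. Kaplan-Meier can hide the difference (Step 2) or run against that arm (Step 3).
- A reader might take one simulated percentage as the size of the error. No duration is documented, and death timing alone moves the figure from substantial to nil.
- A reader might infer that the 25% ceiling is exact. The planning figure is 30-day all-cause mortality. Some deaths may follow discharge, and more may follow discharge from the ICU than from the hospital.

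**Weight.** The primary mortality comparison, the sample size and the interim boundaries are untouched, and in-hospital mortality will be reported beside length of stay. That lowers the severity; it does not make the Kaplan-Meier median interpretable.

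**Conclusion.** The Kaplan-Meier analysis is wrong as written. It censors a competing event that the plan expects in 50% to 75% of patients, and at the planned IMV mortality its median has no counterpart in real patients unless a third or more of those deaths follow discharge. In the illustrations it gives either equal medians (17.3 days) despite 24.8% v 45.5% discharged alive by day 30, or about 30 v 27 days despite identical survivor stays.

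The Wilcoxon comparison of hospital stay is conditionally at fault. With raw days for all patients and deaths earlier than discharges, it favours the arm with more deaths. Across assumed survivor medians of 15 to 30 days and decedent medians of 8 to 15 days, about 6% to 82% of trials are significant at 118 per arm. For length of ventilation no direction can be claimed. Only secondary endpoints are affected; this should be fixed.

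**What to change.** - Replace the Kaplan-Meier medians with the cumulative incidence of discharge alive from hospital and from ICU, with death as a competing event: Aalen-Johansen estimate, with Gray's test or a Fine-Gray model.
- In place of the Wilcoxon tests on raw durations, test hospital-free days and the already listed ventilator-free days, each with death = 0, and state the time horizon.
- In the seven-day SOFA comparison, rank death before day 7 as worst.
- Report raw hospital stay and ventilation time in survivors, descriptively only.

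**Cost.** Wording in the analysis plan and some programming, with no new patients or visits. Data collection and follow-up already covers length of stay, hospital survival and 30-day survival, with daily records to day 30. The change should be made before any unblinded look at these endpoints.

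**Downside.** A measure that includes death partly reflects mortality. In a simulated case with assumed mean time to death 10 days, mean survivor stay 20 days and 88 per arm, a worst-rank test rejected in about 92% of trials although survivors' stays were identical. Such results should stand beside mortality and not be read as a separate effect on stay.

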## Abstract

**Background:**

Acute respiratory failure (ARF) is still one of the most severe complications in immunocompromised patients. Our previous systematic review showed noninvasive mechanical ventilation (NIV) reduced mortality, length of hospitalization and ICU stay in AIDS/hematological malignancy patients with relatively less severe ARF, compared to invasive mechanical ventilation (IMV). However, this systematic review was based on 13 observational studies and the quality of evidence was low to moderate. The efficacy of NIV in more severe ARF and in patients with other causes of immunodeficiency is still unclear. We aim to determine the efficacy of the initial ventilation strategy in managing ARF in immunocompromised patients stratified by different disease severity and causes of immunodeficiency, and explore predictors for failure of NIV.

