Two indications have been mainly considered for NIV in patients with relatively severe ARF: (1) alternative to IMV when ARF patient has contraindications to IMV, and (2) to avoid IMV when ARF patient has not yet met the criteria for intubation [20]. Generally, indications for NIV treatment include increased dyspnea (moderate to severe), tachypnea (with respiratory rate > 24 breaths per min in obstructive or >30 per min in restrictive), the use of accessory muscles, or paradoxic abdominal movements. Other indications include acute or acute on chronic ventilatory failure with hypercapnia and respiratory acidosis (PaCO_2_ > 45 mmHg and pH <7.35) and/or hypoxemia PaO_2_/FiO_2_ ratio < 200 [8]. Respiratory arrest and inability to fit the mask are considered absolute contraindications to NIV. Relative contraindications include: medically unstable (e.g. shock, uncontrolled cardiac events and uncontrolled upper gastrointestinal hemorrhage), uncooperative and agitated, uncontrolled excessive secretions, multiple organ failure, recent upper airway surgery [8].

NIV is not appropriate for all immunocompromised patients with ARF either [21, 22]. Efficacy of NIV on patients depends on disease severity, causes of immunodeficiency and forms of ARF. It’s critically important to select target patients carefully. Recently, we and our collaborators conducted a systematic review and meta-analysis [21] based on 13 observational studies (2552 patients). The study showed NIV could significantly reduce mortality, duration of hospitalization/ICU stay, and nosocomial infections mainly in less severe (reflected by the Simplified Acute Physiology Score II [23], SAPS II < 60), AIDS, and hematological malignancy subgroups, with quality of evidence from very low to moderate. However, NIV didn’t show any significant advantages over IMV in relatively more severe patients [21]. To our knowledge, evidence for other causes of immunodeficiency and different types of ARF is lacking. Early recognition of failure of NIV is also important for prognosis in these patients. Several predictors of NIV failure have been proposed to be used in immunocompromised patients, such as higher disease severity, higher respiratory rate under NIV, delayed initiation of NIV treatment, need for vasopressors or renal replacement therapy [24]. However, the cut-off point of transferring NIV to IMV in these patients is still unclear [25].

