The primary goal of the present multicentre randomized controlled trial is to assess the efficacy of the initial ventilation strategy, NIV or IMV, in managing severe hypoxemic ARF in immunocompromised patients. The secondary goal of this trial is to assess the effect of NIV or IMV in patients stratified by different disease severity, causes of immunodeficiency, and presence of predictors for failure of NIV.

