#### Secondary endpoints

In-hospital mortality.Length of stay in hospital.Length of mechanical ventilation.Nosocomial infections (diagnosed according to the criteria of Centers for Diseases Control and Prevention [34]).Seven-day organ failure as indicated by the Sequential Organ Failure Assessment score.Adverse events of intervention (such as facial ulceration, stomach dilatation).Failure of mechanical ventilation: The transfer of NIV to IMV as well as death within 30 days in NIV group will be considered as failure of NIV; Death within 30 days in IMV group will be considered as failure of IMV.)Improvement of oxygenation: increase of oxygenation index by 100 compared to baseline or to 200 and above after 45 min of mechanical ventilation.Continuous improvement of oxygenation: Improvement of oxygenation could be maintained till weaning or transfer of mechanical ventilation. Proportion of patients intubated at 30 days (both groups). Proportion of patients intubated and weaned at 3 days (both groups). Ventilator-free days Proportion and timing of tracheostomy.

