## Conclusion

In conclusion, VENIM is the first randomized controlled trial aiming at assessing the initial ventilation strategy, NIV or IMV, in treating moderate and severe acute respiratory failure in immunocompromised patients, stratified by disease severity, causes of immunodeficiency, and exploring the predictors of NIV failure. The result of this RCT may help doctors with their ventilation decisions.

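### The only model for predictors of NIV failure uses intubation as its outcome, so an NIV patient who dies by day 30 without intubation counts as a non-event

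*Protocol article*

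**What the plan says.** The Background of the Abstract gives one aim as to "explore predictors for failure of NIV", and the Conclusion repeats it ("exploring the predictors of NIV failure").

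Under Study outcomes, Secondary endpoints, NIV failure is a composite: "The transfer of NIV to IMV as well as death within 30 days in NIV group will be considered as failure of NIV". I read this as either event counting. In the IMV group the same item counts death within 30 days alone as failure.

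Under Statistical analysis, Secondary endpoints, the composite (failure of mechanical ventilation) gets a between-group χ² test and subgroup analyses like those for the primary endpoint. The modelling text is separate. It starts with "Intubation rate in NIV group and weaning rate in IMV group will be reported as absolute and relative frequencies" and continues: "Independent variables associated with intubation rate and weaning rate will be explored with Logistic analysis model". Selection is stepwise, and ventilatory approach and disease severity are both forced in. No other predictor model appears in the article.

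**The concern.** The aim, the definition and the model do not line up. The aim concerns NIV failure and the definition includes death by day 30, but for NIV patients the model sees only intubation. A patient who dies suddenly on NIV, whose care is limited after entry, or who is weaned from NIV and then dies before day 30 is placed with the patients for whom NIV worked.

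Death is not a rare event here, since the Sample size section plans for 50% 30-day mortality under NIV. A factor linked to death without intubation could look weaker than it is as a predictor of failure. The Discussion stresses patient selection for NIV, and the Conclusion hopes the result will help doctors with ventilation decisions, so the model should answer the question the article poses.

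**Working it through.** **Text comparison**

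| Event in an NIV patient by day 30 | NIV failure as defined | Event in the intubation model |
|---|---|---|
| Transferred to IMV, survives | Yes | Yes |
| Transferred to IMV, dies | Yes | Yes |
| Never intubated, dies | Yes | **No** |
| Never intubated, survives | No | No |

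The definition and the model disagree in the third row only.

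**How many patients could be in that row?** The plan states no figure to reproduce, so what follows is an illustration.

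Inputs from the article:
- total 236, allocated 1:1 (Randomization and blinding), so 236 / 2 = 118 per arm;
- NIV mortality 50% (Sample size), so 118 × 0.50 = 59 deaths.

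Input not in the article: the intubation rate in the NIV arm, or the share of NIV deaths without intubation. Both are assumed below.

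*Lower bound for an assumed intubation rate i.* Intubated deaths cannot exceed intubated patients, so deaths without intubation ≥ 118 × (0.50 − i), or 0 if that is negative.
- i = 30%: 118 × 0.20 = 23.6, about 24
- i = 40%: 118 × 0.10 = 11.8, about 12
- i = 50%: 0

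*Number for an assumed share f of deaths without intubation*, with intubation held at 50% (59 patients). Miscoded = 59 × f; composite failure rate = (59 + 59f) / 118.

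| f | Miscoded | Composite failure rate (intubation 50%) | Share of failures missed |
|---|---|---|---|
| 10% | 5.9 | 55% | 9% |
| 20% | 11.8 | 60% | 17% |
| 30% | 17.7 | 65% | 23% |
| 50% | 29.5 | 75% | 33% |

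The range is thus about 0 to about 24-30 of 118. The 118 includes the 25% allowance for loss. On the 88 per arm before that allowance there are 44 deaths, and the same assumptions give 0 to 22.

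**The forced covariate.** If intubation is modelled in the NIV arm, as the preceding sentence implies, ventilatory approach takes one value and its coefficient cannot be estimated. If the arms are pooled, intubation is the assigned treatment in the IMV arm, so arm almost determines the outcome. The model needs rewording on either reading.

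**The case against.** **The number may be close to zero.** Do-not-intubate patients are excluded at entry, and the NIV section under Implementation of interventions sends patients in whom NIV fails to intubation under broad criteria. This stands and is why the lower part of the range is more likely. It does not rule out sudden death, limits on care set after entry, or death after NIV weaning or discharge.

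**Intubation is a sensible outcome.** The Background names the point of transfer from NIV to IMV as an open question, and predictors of intubation speak to that. A composite brings in deaths from the underlying disease after successful weaning. This also stands, and it is the reason to keep intubation as a sensitivity analysis. It does not make intubation the same thing as NIV failure as the article defines it.

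**The composite is analysed elsewhere.** True: by a between-group test and by subgroup. Neither looks for predictors of failure among NIV patients.

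**Stronger readings that the article does not support.**
- A reader might infer that the NIV-versus-IMV comparison will be stratified by factors that arise after randomisation. The secondary goal does speak of patients "stratified by different disease severity, causes of immunodeficiency, and presence of predictors for failure of NIV", and the Background lists candidates such as "higher respiratory rate under NIV, delayed initiation of NIV treatment, need for vasopressors or renal replacement therapy". But that list reports proposals from earlier work and also includes disease severity. The goal does not say which predictors will be used, and the interaction variables under Statistical analysis, Primary endpoint are baseline SAPS II, baseline PaO2/FiO2 and cause of immunodeficiency. No stratification by a post-randomisation factor is planned there.
- A reader might also put a size on the bias. If failure were 40% v 67% and 27% of failures were missed regardless of the predictor, the odds ratio would fall from (0.67/0.33)/(0.40/0.60) = 3.05 to (0.489/0.511)/(0.292/0.708) = 2.32. The arithmetic is right, but none of the inputs comes from the article. They are also strained. With equal-sized predictor groups, failure averages 53.5%, of which 14.4 points are missed and 39 are intubated; at 50% mortality, (50 − 14.4) / 39 = 91% of intubated patients would die, against the 75% planned for IMV. A reversal of a predictor's sign is conceivable, but no calculation supports it.

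**Conclusion.** The mismatch is real and can be read directly from the text: the stated aim is predictors of NIV failure, failure includes death by day 30, and the only predictor model leaves out deaths without intubation. Its size is unknown. It is about 0 to about 24-30 of 118 NIV patients, given the planned 50% mortality and assumed intubation rates of 30-50% or assumed shares of deaths without intubation of up to 50%. No particular bias in any predictor's odds ratio can be claimed.

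The model is exploratory and secondary. The primary comparison, the sample size and the monitoring are not affected. It should still be corrected, because a named aim is not answered by the one model that serves it.

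**What to change.** In Statistical analysis, Secondary endpoints:

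1. For predictors of NIV failure, make the outcome the composite already defined (transfer to IMV or death by day 30), modelled within the NIV arm.
2. Keep intubation alone as a sensitivity analysis, so that predictors of transfer can still be seen.
3. Do not force ventilatory approach into this NIV-only model, where it is constant. Disease severity can stay forced.

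The cost is a change of wording. Transfer to IMV and day-30 vital status are already collected. The small downside is that the composite mixes intubation with deaths from other causes, which the sensitivity analysis helps to separate.
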